## Abstract

**Aim:** The aim was to design a study protocol for evaluating the efficacy of an interactive podcast program to assist Type 1 diabetes patients transitioning from adolescence to young adulthood.

**Design:** The study design is a parallel 1:1 two-arm randomized controlled trial emphasizing treatment fidelity through standardized interventions and improved adherence to reduce biases in outcomes.

**Methods:** This theoretical-based study will be conducted at two medical centers in northern Taiwan, enrolling 88 participants. Participants will be randomly assigned to either the experimental group, receiving the interactive podcast program “Living With Type 1 Diabetes to Grown-Up,” or the active control group, receiving the e-book “Transitioning from Adolescence to Early Adulthood: The Ins and Outs of Type 1 Diabetes.” The 3-month intervention will release 36 podcast episodes at a rate of three per week. Data will be collected at baseline, postintervention, and at 3 and 6 months postintervention to evaluate the efficacy of the intervention on disease control outcomes, emotional distress, diabetes knowledge, self-care behaviors, self-management confidence, interpersonal distress, and family conflict.

**Conclusion:** This first evidence-based, rigorously designed podcast program will offer valuable guidelines for future interventions aimed at helping adolescents with Type 1 diabetes transition to adulthood.

**Impact:** This study's positive findings could support podcasts as an innovative tool for helping adolescents with Type 1 diabetes transition to young adulthood. Additionally, it may provide valuable insights for future research and health policymakers, potentially transforming diabetes management approaches.

**Reporting Method:** The authors adhered to CONSORT guidelines to ensure transparency and reliability.

**Patient or Public Contribution:** There is no patient or public contribution.

**This Paper Contributes to the Wider Global Clinical Community:** This paper provides an evidence-based framework for using podcasts to support self-management and well-being in adolescents with Type 1 diabetes and offers insights for future digital health strategies.

**Trial Registration:** ClinicalTrials.gov identifier: NCT06464640

## 1. Introduction

Although Type 1 diabetes (T1D) accounts for only around 5%–10% of all diabetes cases, its global incidence and prevalence are increasing [1]. According to the US SEARCH for Diabetes in Youth study, T1D incidence was 22.2 per 100,000 in 2018, reflecting a 2.02% increase from 2002 [2]. In 2021, approximately 8.4 million people worldwide lived with T1D, including 1.5 million individuals under the age of 20 [3], with the highest incidence observed between the ages of 10 and 14 [4]. In Taiwan, T1D is most prevalent among individuals aged 0–19, with an incidence rate of 5.17 per 100,000 and a prevalence rate of 0.05% [5]. Given the significant global prevalence of T1D among children and adolescents, healthcare systems must be prepared to address the increasing needs of individuals transitioning from adolescence to early adulthood.

### 1.1. Background

Briefly, the transition from late adolescence to early adulthood is a critical developmental period marked by rapid physiological and psychological changes [6]. It is one of the most stressful periods in human development because it involves significant life experiences, such as making long-term decisions about relationships and careers, leading to uncertainty and fear [6, 7]. This is particularly true for individuals with chronic illnesses, as they must take on greater responsibility for self-care and disease management [8, 9]. Maintaining glycemic control during this period is especially challenging, with only 17% of patients achieving the glycemic control targets set by the American Diabetes Association [10]. Poor glycemic control can increase the risk of micro- and macrovascular complications [11], diabetic ketoacidosis hospitalizations [12], mortality [13], and heightened anxiety [14], adversely impacting sleep and quality of life [15, 16]. Therefore, recognizing the challenges in disease management for T1D patients during their transition period and developing interventions tailored to their needs is critical.

Technology is a key healthcare need of T1D patients aged 16–25 during their transition [17]. Participants emphasize its importance in managing their T1D [14, 17]. Technology-based interventions, such as blood glucose monitoring apps, text messaging, and online educational platforms, have been applied in managing T1D in young people [18, 19]. These interventions have shown significant or potential benefits, such as improved disease control outcomes [19, 20], reduced emotional distress [18], enhanced diabetes knowledge and self-care behaviors [19, 20], increased self-management confidence [18, 19], and decreased interpersonal distress [19] and family conflict [21]. However, inconsistent effects on blood glucose control (HbA1c) and psychological health outcomes [18–20] have also been reported. Lower study quality may have limited the ability of these studies to detect changes [19, 20]. Most importantly, these interventions were not tailored to individual needs and preferences [19].

mHealth applications have become popular among the younger tech-savvy generations, offering innovative approaches to managing chronic conditions and health behaviors [22–25] with the potential to be tailored to individual needs. In Taiwan, 98% of high school students use smartphones, with an average weekly usage of 6.39 days [24]. The proliferation of digital tools has spurred the growth of digital technology, with podcasts being one of the fastest growing digital educational media among adolescents [26]. In the United States, approximately 57% of individuals aged 12 and above have listened to podcasts, with an average weekly listening time of over 6 h [27]. In Taiwan, 16.3% of Internet users regularly listen to podcasts [28], presenting an opportunity to leverage podcast-based interventions to disseminate information [29] to T1D patients during transition.

### 1.2. Existing Literature and Gaps

Podcasts introduced in the early 2000s have gained widespread popularity. Creators upload programs to podcast platforms for on-demand streaming or downloading, offering a mobile platform that supports multitasking [30, 31]. They offer flexible and enjoyable learning experiences that can overcome temporal and spatial constraints, reduce anxiety, enhance motivation, and lead to effective learning outcomes [32–34]. Recently, podcasts have been increasingly integrated into healthcare education to improve clinical practice competencies [35, 36], enhance health-related nutritional literacy among high school students [37], improve parents' ability to assess the trustworthiness of treatment benefit claims [38], and address the complex educational needs of cancer survivors [39].

In the context of diabetes care, existing literature mainly addresses healthcare professionals, outlining treatment guidelines [40], exploring diabetes treatment trends [41], highlighting the importance of language in patient–provider communication for diabetes self-management [42], offering strategies to empower patients [43], and discussing recent advancements in diabetes research [44–46]. Recently, podcasts have started incorporating the perspectives of individuals with Type 2 diabetes [47] presenting as episode transcripts. However, a significant gap exists in using podcast-based interventions to support T1D patients during their transitional phase and improve their disease management and outcomes.

### 1.3. Theoretical Framework

The transition from adolescence to early adulthood involves significant life changes and environmental shifts. According to transition theory, these changes are recognized as antecedents and categorized as developmental, situational, health-illness, and organizational [48, 49]. Developmental transitions occur as individuals progress through different stages of human development. Situational transitions involve changes in context, such as education or occupation, resulting in shifts in personal roles or relationships. Health-illness transitions refer to changes in health status. Organizational transitions involve changes in institutional settings, such as care models. Nursing interventions are critical during these transitions, helping individuals achieve desired outcomes, including well-being (physical and psychological comfort), mastery (an individual's ability to manage and control their new situation or condition effectively), and relationship comfort (the quality and stability of family relationships) [49].

In this study, we focus on adolescents transitioning into early adulthood, following the framework of Chick and Meleis [48] and Schumacher and Meleis [49], identifying four types of transitions: developmental, situational, health-illness, and organizational. The intervention utilizes an interactive podcast program, “Living with Type 1 Diabetes to Grown-Up,” which explores outcomes of well-being (disease control outcomes and emotional distress), mastery (diabetes knowledge, self-care behaviors, and self-management confidence), and relationship comfort (interpersonal distress and family conflict).

The interactive component of the intervention applies the self-regulation theory's PRIDE steps—problem identification, research into daily activities, goal identification, plan development, and self-reward mechanisms—commonly used in adolescent and disease self-management research [50]. Participants provide audio feedback according to study guidelines and steps, with downloadable responses from the research team.  Figure 1 illustrates the theoretical framework.

## 2. The Study

### 2.1. Aims

This study will implement rigorous treatment fidelity (TF) monitoring to evaluate the efficacy of the interactive podcast program, “Living with Type 1 Diabetes to Grown-Up” on disease control outcomes, emotional distress, diabetes knowledge, self-care behaviors, self-management confidence, interpersonal distress, and family conflict at baseline, postintervention, and 3 and 6 months postintervention.

### 2.2. Hypotheses

Based on the prior efficacy of apps and internet-based interventions [18, 19, 21], we hypothesized that participants in the experimental group receiving the interactive podcast program, “Living with Type 1 Diabetes to Grown-Up,” would demonstrate better disease control outcomes, along with improved diabetes knowledge, self-care behaviors, and self-management confidence, compared to those in the active control group. We also hypothesized that emotional distress, interpersonal distress, and family conflict would be lower in the experimental group compared to the active control group.

### 2.3. Developing the Podcast Intervention

From August 2023 to July 2024, the podcast intervention was developed and tested using the design science research framework of Hevner [51], emphasizing a user-centered approach. The development process comprised three key cycles: relevance, rigor, and design. The relevance cycle was shaped by insights from previous qualitative studies [14] and a Delphi study [17]. The rigor cycle involved an extensive literature review, and the results from both prior cycles were integrated into the design cycle. Content creation adhered to international quality guidelines for podcast production [52]. Usability was assessed through heuristic evaluation [53], think-aloud protocols [54], and measures of user interaction satisfaction [55], resulting in a final satisfaction score of 4.86 (± 0.33) [56]. The findings from these preliminary studies informed the development of the intervention, as detailed in Section 3.4.

## 3. Methods

### 3.1. Study Design

This study is a double-blind, parallel, 1:1 randomized controlled trial (RCT). After enrollment assessments, participants will be randomly assigned to either the experimental group, receiving the interactive podcast program, “Living with Type 1 Diabetes to Grown-Up,” or the active control group, receiving a sham treatment using an ineffective e-book, “Transitioning from Adolescence to Early Adulthood: The Ins and Outs of Type 1 Diabetes” which will be given at enrollment [57]. Both interventions will last for 3 months. Outcome measures will be evaluated at four time points: pre-randomization (T0), immediately postintervention (T1), 3 months post-intervention (T2), and 6 months postintervention (T3). This study has been registered at ClinicalTrials.gov (under identifier NCT06464640).  Figure 2 shows the detailed study process.

### 3.2. Study Setting

Participants will be recruited from the pediatric and adult endocrinology outpatient clinics and wards of two medical centers in northern Taiwan specializing in youth T1D treatment. The combined annual patient pool at these centers includes approximately 350 eligible candidates. We anticipate approaching approximately four eligible patients per week, with an expected refusal rate of 20% following the COVID-19 pandemic to recruit 12–16 participants per month [57]. We aim to recruit 88 participants (as per the sample size calculation detailed below) within a maximum of 6–8 months. Should unforeseen challenges, such as another public health crisis, arise, we will extend the recruitment period or explore additional recruitment sites as contingency measures.

### 3.3. Participants

#### 3.3.1. Eligibility Criteria

Participants will be recruited using convenience sampling. Inclusion criteria are as follows: (1) diagnosed with T1D by an endocrinologist before the age of 16, with a disease duration of more than 6 months, allowing sufficient time for diagnosis stabilization and self-care training [58, 59]; (2) aged between 16 and 25, representing the transition period from late adolescence to early adulthood [58, 60]; (3) mean HbA1c level ≥ 7.5% in the year before inclusion to identify patients who have inadequate blood sugar control, making them suitable candidates for the podcast intervention; (4) the ability to communicate in Mandarin or Taiwanese; (5) possession of a smartphone, tablet, or computer with Internet access, enabling program transmission and voice interaction for data collection; and (6) willingness to participate in the study with signed informed consent. For minors, the legal guardian must also provide signed informed consent. Individuals with other metabolic diseases, chromosomal abnormalities, major illnesses, or significant auditory and cognitive impairments will be excluded from this study, as these conditions may affect their healthcare needs and influence their understanding and utilization of the intervention [61, 62]. Participants using continuous glucose monitoring (CGM) will also be excluded from the trial, as its adoption remains low in Taiwan due to high out-of-pocket costs despite partial reimbursement [63]. This ensures consistency in glycemic data sources.

#### 3.3.2. Sample Size Calculation

Few studies have explored podcast-based interventions for chronic diseases or illnesses in adolescents. As podcasting is a technology-based intervention method, results from our prior study of Healthcare CEO App [57] were used for sample size calculation. Effect sizes were calculated using Cohen's *d*. For groups of 19 participants each, the mean HbA1c for the experimental vs control group at 3, 6, and 9 months postintervention was 7.93 ± 1.36 versus 8.69 ± 2.40, 8.30 ± 1.29 versus 8.82 ± 2.69, and 8.24 ± 1.58 versus 8.87 ± 2.72, respectively, yielding an effect size of 0.38, 0.26, and 0.32, respectively.

Using G-Power 3.1.9.4 software, the required sample sizes were calculated for each group across the three time points as 18, 38, and 26 participants, respectively. Assumptions included two groups with four repeated measures, *α* set at 0.05, power at 0.80, and a correlation coefficient of 0.5. No participants withdrew from our prior study [57]. However, considering a conservative dropout rate of 12% based on similar online intervention studies with a 6-month follow-up period [64], the number of participants was increased to 21, 44, and 30 per group. The maximum sample size calculated based on the smallest effect size at T2 was chosen. Therefore, the total sample size will be 88 participants.

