#### 3.5.2. Active Control Group: Sham Treatment

Our previous study demonstrated that e-books did not have a significant impact on glycemic control (HbA1c: 8.30 ± 1.29 vs. 8.82 ± 2.69, *p* = 0.477), diabetes knowledge (16.59 ± 3.26 vs. 15.42 ± 3.85, *p* = 0.336), self-care behaviors (152.94 ± 13.38 vs. 155.95 ± 14.56, *p* = 0.525), self-management confidence (29.82 ± 4.30 vs. 27.63 ± 5.82, *p* = 0.212), or interpersonal distress (11.00 ± 5.01 vs. 10.53 ± 6.54, *p* = 0.811) after 6 months in our prior trial [57]. Therefore, the active control group will receive the e-book “Transitioning from Adolescence to Early Adulthood: The Ins and Outs of Type 1 Diabetes,” compiled from the Healthcare CEO app collection, as a sham treatment. This title and content indicate its suitability as a minimally active control that is thematically relevant [66, 67]. The topics in the e-book include (1) diabetes knowledge, (2) how to manage your blood sugar, (3) eating and exercising well, (4) healthy interpersonal relationships, (5) parent–child harmony, and (6) you are not alone. Each unit includes recommended readings, such as “Needles” and “My Life Is Not Controlled by Diabetes.” Although parts of the themes are similar, the e-book is simplified to 600–800 words of pure text per unit, lacking T1D patient experience sharing and interactive engagement. Participants in the active control group will not be reminded to read the e-book, no additional interventions or consultations will be provided, and no follow-up calls will be made during the intervention. After the study, participants in the active control group will be offered the opportunity to listen to all podcast episodes and receive the same incentives as the experimental group, if desired. The intervention characteristics of the experimental and active control groups are presented in Table 3.

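### The effect sizes behind N = 88 do not follow from the printed HbA1c data: the value that sets N is about 0.25, not 0.26, and power after the planned dropout is about 75–77% by the calculation that reproduces the plan's sizes

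*Protocol article*

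**What the plan says.** Section 3.3.2 of the protocol article bases the sample size on HbA1c from the team's earlier app trial. It states that "Effect sizes were calculated using Cohen's *d*" and introduces the data with "For groups of 19 participants each". The HbA1c results at 3, 6 and 9 months (experimental versus control) are "7.93 ± 1.36 versus 8.69 ± 2.40", "8.30 ± 1.29 versus 8.82 ± 2.69" and "8.24 ± 1.58 versus 8.87 ± 2.72", "yielding an effect size of 0.38, 0.26, and 0.32, respectively".

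With two groups, four repeated measures, alpha 0.05, power 0.80 and correlation 0.5, the section reports 18, 38 and 26 per group. A 12% dropout allowance raises these to 21, 44 and 30. The largest, driven by the smallest effect size, is chosen: 44 per group, 88 in total. The same paragraph says "No participants withdrew from our prior study".

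Section 3.5.2 repeats the 6-month HbA1c comparison with p = 0.477. It adds 6-month questionnaire results from the same trial, among them diabetes knowledge, "16.59 ± 3.26 vs. 15.42 ± 3.85", p = 0.336.

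**The concern.** The effect sizes are the only empirical input to N, and everything needed to check them is printed. The 6-month value is the one that fixes 88. If it is overstated, the plan's own rule asks for more participants than it enrols, and the stated 80% power is not met after the dropout the plan itself allows for. The section on the control condition also appears to contradict the group sizes on which the effect sizes are said to rest.

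**Working it through.** **1. Effect sizes from the printed figures, 19 per group**

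d = difference / pooled SD, with pooled SD = √((SD₁² + SD₂²)/2) for equal groups.

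| Visit | Difference | Pooled SD | d | Stated | Difference / 2.0 |
|---|---|---|---|---|---|
| 3 months | 0.76 | √((1.36² + 2.40²)/2) = 1.95 | 0.390 | 0.38 | 0.38 |
| 6 months | 0.52 | √((1.29² + 2.69²)/2) = 2.11 | 0.2465 | 0.26 | 0.26 |
| 9 months | 0.63 | √((1.58² + 2.72²)/2) = 2.22 | 0.283 | 0.32 | 0.315 |

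Rounding does not explain the gap. Moving each printed figure by ±0.005 allows only 0.241–0.252 at 6 months and 0.278–0.288 at 9 months. Other definitions do not give the set either:
- simple average of the two SDs: 0.40, 0.26, 0.29
- Hedges' g: 0.38, 0.24, 0.28
- control-group SD: 0.32, 0.19, 0.23

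Of the divisors tried, only a common 2.0 gives all three stated values.

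**2. Reproducing the plan's sample sizes**

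The article names no test. The repeated-measures ANOVA between-factors F test reproduces its figures if the stated d is entered directly as Cohen's f. Its noncentrality is λ = f²·N·m / (1 + (m − 1)ρ). With m = 4 and ρ = 0.5 this is λ = 1.6·f²·N, on 1 and N − 2 degrees of freedom.

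- f = 0.38 gives 18 per group.
- f = 0.26 gives 38 per group (power 0.808 at N = 76).
- f = 0.32 gives 25 per group, but the unrounded 0.315 gives the printed 26.

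Dividing by 0.88 and rounding up gives 21, 44 and 30, as printed. The match at 0.315 is further support for the common divisor of 2.0.

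**3. Numbers analysed at 6 months**

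Whole-number questionnaire totals restrict the possible means.

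- Experimental arm with n = 19: the nearest possible means are 315/19 = 16.58 and 316/19 = 16.63 (printed 16.59); 566/19 = 29.79 and 567/19 = 29.84 (printed 29.82); 2905/19 = 152.89 and 2906/19 = 152.95 (printed 152.94). None fits.
- Experimental arm with n = 17: 282/17 = 16.59, 507/17 = 29.82, 2600/17 = 152.94 and 187/17 = 11.00. All fit. Among sizes from 14 to 22, only 17 fits all four.
- Control arm with n = 19: 293/19 = 15.42, 2963/19 = 155.95, 525/19 = 27.63 and 200/19 = 10.53. All fit.

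Pooled t-test p-values agree:

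| Outcome | Printed p | 17 vs 19 | 19 vs 19 |
|---|---|---|---|
| HbA1c | 0.477 | 0.473 | 0.452 |
| Knowledge | 0.336 | 0.335 | 0.319 |
| Self-care | 0.525 | 0.524 | 0.511 |
| Confidence | 0.212 | 0.212 | 0.195 |
| Interpersonal distress | 0.811 | 0.812 | 0.805 |

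For HbA1c, rounding of the printed figures allows 0.443–0.462 with 19 versus 19, which excludes 0.477. With 17 versus 19 it allows 0.464–0.483, which includes it.

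If HbA1c was analysed on 17 versus 19, the pooled SD is √((16·1.29² + 18·2.69²)/34) = 2.148, and d = 0.52/2.148 = 0.242.

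**4. Consequence, by the calculation in step 2**

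| 6-month value | Needed per arm | With 12% dropout (total) | Power, 38 per arm | Power, 88 × 0.88 = 77.44 in total | Power, all 88 |
|---|---|---|---|---|---|
| 0.26 (stated) | 38 | 44 (88) | 0.808 | 0.815 | 0.862 |
| 0.2465 (19 vs 19) | 42 | 48 (96) | 0.765 | 0.773 | 0.824 |
| 0.242 (17 vs 19) | 43 | 49 (98) | 0.750 | 0.758 | 0.811 |

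**5. The separate conversion problem**

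For two equal groups f = d/2. With f = 0.2465/2 = 0.123 and 38 per arm, power is about 0.27.

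**The case against.** The shift from 0.26 to 0.25 or 0.24 is small: 3 to 5 points of power, or 8 to 10 participants. It sits inside a calculation that has a much larger fault, the entry of d as f. The test is inferred. The average of the two SDs, 1.99, also gives 0.26 for the value that matters. All of this is fair as to size. It does not restore the stated figures, because no definition of d tried here gives all three, and a repair of the d-to-f step must still start from the right d.

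Three stronger readings are tempting, and the documents do not support them.

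- A reader might infer that 44 per arm misses 80% outright. By this calculation 44 analysed per arm gives 81–82%. The shortfall appears only after the full 12% is removed. Because the planned GEE analysis follows intention-to-treat, participants with some visits may still contribute data.
- A reader might infer that the dropout allowance overlooks missing data in the prior trial. If 19 were enrolled per arm, the implied 6-month loss is 2/19 = 10.5% in one arm and 2/38 = 5.3% overall. The planned 12% exceeds both.
- A reader might infer that the no-withdrawal statement is false. A smaller number analysed can mean a missed visit or questionnaire, not a withdrawal.

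The evidence for 17 versus 19 is also weaker for HbA1c than for the questionnaires. The whole-number check cannot be applied to it, and p = 0.477 also fits 17 versus 17. That alternative leaves d at 0.2465, since equal group sizes give the same pooled SD. Nothing printed gives the numbers analysed at 3 or 9 months.

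**Conclusion.** The point holds as a limited arithmetic error in the input that sets N. The stated effect sizes do not follow from the printed means and SDs. The 6-month value is 0.2465 with 19 per group, or 0.242 if HbA1c was analysed on 17 versus 19. The statement of 19 per group also conflicts with the 6-month results in section 3.5.2.

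The size given, 75–77% power after the planned dropout against the stated 80%, rests on the inferred F test with d entered as f, four measures, correlation 0.5, and 12% lost from each arm. It is not an estimate of the trial's true power: the conversion error is a separate and far larger matter. The difference in the 3-month effect size changes no decision, and the overstated 9-month value does not set N.

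**What to change.** In section 3.3.2:

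1. Recalculate the three effect sizes from the printed data and the numbers actually analysed. With 19 per group they are 0.39, 0.25 and 0.28.
2. Give the number analysed per arm at each visit of the prior trial, and reconcile the 19 per group with the 6-month results in section 3.5.2.
3. Reconcile the no-withdrawal sentence with those numbers, for example by separating withdrawal from missing visits.
4. Name the test used, and restate the power that 88 provides after the planned 12% dropout, with the correct conversion from d to f.

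The cost is one rewritten paragraph and a less favourable stated power. N can stay at 88 if the lower power is disclosed. If the plan's rule for choosing N is kept as it stands, the corrected input alone moves the total to 96–98.

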### 3.8. Statistical Analysis

Descriptive statistics such as frequency distribution, percentage, mean, standard deviation, and maximum/minimum scores will be utilized to characterize the subjects' demographics, disease characteristics, outcome variables at enrollment, and podcast usage. The efficacy of the intervention will be assessed using generalized estimating equation (GEE) modeling, which accommodates repeated measurements and deals with missing data effectively, following the intention-to-treat principle.

GEE will evaluate differences in outcome variables between experimental and control groups over time. Linear GEE models will be applied for all the continuous outcomes. The models will include fixed effects for the group (experimental vs. control), time (baseline, postintervention, and 3 and 6 months postintervention), and their interaction. The working correlation structure will be selected based on the quasi-likelihood under the independence model criterion [77]. Statistical significance will be determined at *p* < 0.05. All analyses will be conducted using IBM SPSS 26.0 for Windows.

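### The stated 80% power at Cohen's d = 0.26 does not follow from the plan's own inputs; with 88 participants it is about 20% to 33% for the tests the plan points to

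*Protocol article*

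**What the plan says.** Section 3.3.2 of the protocol article bases the sample size on HbA1c in an earlier app trial with 19 participants per group. It states "Effect sizes were calculated using Cohen's" d and prints experimental versus control values of "7.93 ± 1.36 versus 8.69 ± 2.40", "8.30 ± 1.29 versus 8.82 ± 2.69" and "8.24 ± 1.58 versus 8.87 ± 2.72" at three follow-ups, "yielding an effect size of 0.38, 0.26, and 0.32, respectively".

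G*Power was then run for two groups and four repeated measures, with alpha "set at 0.05, power at 0.80, and a correlation coefficient of 0.5". The result: "the required sample sizes were calculated for each group across the three time points as 18, 38, and 26 participants, respectively". Allowing for 12% dropout these become 21, 44 and 30. The largest, driven by the smallest effect, sets the total of 88. No conversion from d to another effect-size scale is mentioned.

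Section 3.8 analyses the outcomes by GEE: "The models will include fixed effects for the group (experimental vs. control), time (baseline, postintervention, and 3 and 6 months postintervention), and their interaction".

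**The concern.** The repeated-measures ANOVA routines in G*Power take Cohen's f. With two equal groups f = d/2, so a d of 0.26 is an f of 0.13. In these routines the required sample size varies roughly with 1/f², so using 0.26 where 0.13 belongs makes it about four times too small.

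This calculation alone sets the size of the trial. If the podcast did exactly as well as the earlier app, a non-significant HbA1c result would be the likely outcome. A reader told that power was 80% would tend to take that result as evidence that the podcast does not work.

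**Working it through.** **Inputs.** From section 3.3.2: m = 4 measures, r = 0.5, alpha 0.05 (F test, taken as two-sided), power 0.80, 12% dropout, and the printed means and SDs. From section 3.1: 1:1 allocation.

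**1. Reproducing the plan's figures.** For the between-factors test with total N, the noncentrality is λ = f²·N·m / (1 + (m − 1)r) = f²·N·4/2.5 = 1.6·f²·N, with 1 and N − 2 degrees of freedom.

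| Value used as f | Smallest n per group with power ≥ 0.80 | Stated |
|---|---|---|
| 0.38 | 18 | 18 |
| 0.26 | 38 (power 0.81) | 38 |
| 0.315 | 26 | 26 |
| 0.32 (as printed) | 25 | 26 |

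The value 0.315 is 0.63/2, which rounds to the printed 0.32. Dropout: 38/0.88 = 43.2, rounded up to 44 per group, 88 in total. This agrees with the plan.

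**2. What the printed data give.** d = difference / √((SD₁² + SD₂²)/2).

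- First follow-up: 0.76/1.95 = 0.39
- Second follow-up: 0.52/2.11 = 0.25 (0.52/1.99 = 0.26 if the two SDs are simply averaged)
- Third follow-up: 0.63/2.22 = 0.28

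At the deciding time point f = d/2 is therefore 0.12 to 0.13. The 0.26 fits the label d; it cannot be an f for these data.

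**3. The same test with f = 0.13.**

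- N = 76: λ = 1.6 × 0.0169 × 76 = 2.06, power 29%.
- N = 88: λ = 1.6 × 0.0169 × 88 = 2.38, power 33%.
- Power of 80% needs 147 evaluable per group. For d = 0.38 and 0.32 the corresponding figures are 69 and 97.

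**4. Group-by-time contrasts in the GEE.** For change from baseline to T2, in SD units, SE = √((2/n)·2(1 − r)) = √(2/n) at r = 0.5.

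- n = 38: SE = 0.229, 0.26/0.229 = 1.13, power 20%.
- n = 44: SE = 0.213, 0.26/0.213 = 1.22, power 23%.

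For the 3-df interaction with d = 0, 0.38, 0.26 and 0.32 over the four occasions, λ = 3.19 (n = 38) or 3.70 (n = 44), and power is 29% or 33%.

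**5. Effect detectable with 80% power, 38 per group.** d is about 0.51 for the group effect averaged over the four occasions and about 0.65 for the T2 change contrast. At the printed pooled SD of 2.11 these are 0.51 × 2.11 = 1.1 and 0.65 × 2.11 = 1.4 HbA1c points, against the 0.52 seen in the earlier trial.

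**The case against.** **The cause is not documented.** A reader might infer that d was simply typed into the f field. The article does not print the value entered, so it does not establish this. The three values are also exactly half the raw mean differences (0.76/2, 0.52/2, 0.63/2). That is what f would be with a within-group SD of 1, later mislabelled as d; it is equally what d would be with a common SD of 2.0, which the article does not mention. The document cannot separate these readings. All of them leave the true f at about 0.12 to 0.13, so the power result is unaffected.

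**Another routine comes close.** The within-between interaction option with f = d/2 gives 20, 41 and 28 per group. It matches none of the stated figures and has 77% power at N = 76. It also treats a between-group d at one time point as an interaction f. For the printed effects (0, 0.38, 0.26, 0.32; mean 0.24) the interaction f is ½·√(0.084/4) = 0.072, not 0.13.

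**Dropouts contribute data.** This stands in part. The intention-to-treat GEE uses partial records, so 76 is a lower bound on the information and the fair statement runs up to the figures for 88.

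**The confirmatory term is not named.** This also stands. Section 3.8 lists group, time and interaction terms without saying which one decides. A reader might take the interaction to be the declared primary test; that is plausible but not stated, so both kinds of test are shown above.

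**A higher correlation would help.** With r = 0.7 (an assumption), power for the T2 change contrast with 38 per group is about 30%. Averaging three follow-ups with baseline adjustment, which section 3.8 does not plan, gives 42% to 47% at r = 0.5. Neither approaches 80%.

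**Conclusion.** The point holds. The 80% power stated for d = 0.26 with 38 evaluable per group is wrong on the plan's own inputs. At r = 0.5 and two-sided alpha 0.05, power is about 29% to 33% for the averaged group effect that appears to have been sized, 20% to 23% for the T2 change contrast, and 29% to 33% for the 3-df interaction. The lower figure in each range is for 76 evaluable, the upper for all 88.

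This rests on d = 0.26 being the planning effect, as the article says. The explanation for the error is an inference, and the conclusion does not depend on it.

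Two secondary points leave the conclusion unchanged. The sized test averages over the pre-randomization measure, where randomized groups should not differ systematically. And the pooled d values from the printed data (0.39, 0.25, 0.28) differ slightly from those stated.

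A reader might go on to infer that the trial must be enlarged. That does not follow: whether to run it at 88 with its real power, or larger, is for the sponsor to decide.

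**What to change.** In section 3.3.2:

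- Remove the claim of 80% power at d = 0.26.
- Recompute d from the printed means and SDs, or state the SD that was used, and say on which scale (d or f) the effect size was entered.
- Name the GEE contrast on which the power statement rests. Give its power at d = 0.26 (about 20% to 33% at r = 0.5, depending on the contrast and on dropout).
- Give the effect detectable with 80% power for that contrast. With 38 per group this is d of about 0.65 for T2 change, or about 0.51 for the averaged group effect.
- State that a non-significant HbA1c result will be reported with its confidence interval and not read as absence of effect.

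The detectable effect should refer to an analysis that section 3.8 actually contains. A baseline-adjusted comparison at T2, for example, is not planned there, and quoting its detectable effect would create a new mismatch.

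The cost is a rewritten paragraph and a much less favourable stated power. No additional participants are required.
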